### Exclusion Criteria

Patients will be excluded if they present the following exclusion criteria:
(1)have undergone mixed hemorrhoids surgery or combined with other operations;(2)women in pregnancy, lactation, and menstruation;(3)with rectal cancer, rectal polyps, tuberculosis, Crohn's disease, and other anorectal diseases;(4)with glucose-6-phosphate dehydrogenase (G6PD) deficiency, inadequate conditions of butyrylcholinesterase enzyme, methemoglobinemia, and myasthenia gravis;(5)with severe respiratory, digestive, cerebrovascular disease, and obvious abnormal liver and kidney functions;(6)with urinary system diseases such as prostate hyperplasia, neurogenic bladder, urethral injury, urethral stricture; and(7)with ulcers, injuries, infections, scars, and allergies in the abdomen.

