### Blinding

All patients will be informed to be equally allocated to the treatment group and control group before enrollment. Blinding of moxibustion is quite difficult to achieve. The treatment will be performed by trained and experienced moxibustion members. Surgeons, moxibustion practitioners, and patients will not be blinded due to the limitation of treatment, while outcome assessors and statisticians will be blinded to treatment allocation.

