#### Secondary Outcomes

(1)Time to first urination: the time from the end of the operation to the first urination.(2)Catheterization rate: the number of people who need catheterization in 24 h after operation in each group, catheterization rate = number of catheterization people/number of people included in each group.(3)Incidence of urinary tract infection (UTI): the occurrence of urinary tract infection during hospitalization, rate = number of infections/number of people included in each group.(4)Length of hospitalization: The average length of hospitalization of patients.(5)Adverse effects: Potential AEs may occur during the study. Patients may suffer from empyrosis, itching, allergy, dizziness with moxibustion and orthostatic hypotension, headache, dizziness, and vomiting with tamsulosin. The supervisor will manage the intervention, and any suspected AEs will be discussed with the principal investigator of the project team. If the patient shows any discomfort or changes in their condition, they are instructed to inform the investigators. The physician will provide the necessary treatment to alleviate any AEs.

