### Statistical Methods

Full analysis set (FAS) and per-protocol set (PPS) will be both used for statistical analysis in this study. In FAS, for missing outcome data, multiple imputations will be used o. For continuous data, they will be represented as mean ± standard deviation and frequency or percentage for categorical data. Statistics will be analyzed with SPSS 22.0 (SPSS Inc., Chicago, IL). For primary outcomes, the chi-square test will be applied to analyze the POUR incidence. For secondary outcomes, the comparison of UTI incidence, AEs, and catheterization rate will be analyzed by the chi-square test; the independent-sample *t*-test or Mann–Whitney *U* test for intergroup comparison will be used for the time to first urination and the length of hospitalization after considering the normality and homogeneity. The dropout rates will be analyzed by the chi-square test, and the impact of the dropout rate will be further analyzed by comparing dropout reasons, characteristics of dropout cases between groups, and the results using intention-to-treat and per protocol. Statistical testing is two-sided, and *p* < 0.05 is considered statistically significant.

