## Discussion

Many risk factors in anorectal surgery, such as anesthesia, surgical stimulation, or pain, can easily cause spasms of the bladder neck and urethral sphincter or weak contraction of the bladder detrusor, inducing reflex dysuria and a high incidence of POUR. POUR is a common urological emergency, which occurs 6–8 h after hemorrhoidectomy, manifested with urgency, lower abdominal pain, distress, refusal to press, and bladder enlargement. Therefore, how to effectively prevent POUR after hemorrhoidectomy is important.

Tamsulosin hydrochloride is a superselective *α*-1a receptor blocker, and it could block *α*1a adrenergic receptors in the prostate and relax the smooth muscle of the prostate, thus improving dysuria and other symptoms. The incidence of postural hypotension is relatively low due to the high selectivity of this drug. It can not only effectively treat urinary retention, and could also reduce the incidence of POUR (23, 24), yet with certain side effects, including dizziness, headache, syncope, and retrograde ejaculation (25).

In China, moxibustion is a commonly used therapy for urinary retention. Moxibustion is an external treatment based on TCM theory. By baking acupoints with burning moxa wool, it is characterized by simple operation, painless, fewer side effects, and stable efficacy. It has been used for more than 2,500 years, and it could dredge meridians and regulate qi-blood to prevent and cure diseases according to TCM theory. By burning moxa without flame over the acupoints, patients will get a warm feeling when close to the body. Its thermal effects, radiation effects, and pharmacological actions (26) could function as an analgesic, alleviating inflammation and enhancing immunity.

Clinical studies have proved that moxibustion could effectively improve urination disorder (27–29), yet there are few highly designed clinical trials to prove its effects in preventing POUR in hemorrhoidectomy. Therefore, we designed a randomized controlled clinical study to compare the difference of prophylactic moxibustion with tamsulosin in reducing the incidence of POUR against patients of hemorrhoidectomy in 24 h and to clarify the efficacy of moxibustion to prevent POUR.

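### Adverse effects are tested between arms, but the only stated way of detecting them is that unblinded patients speak up, so unequal reporting could look like a safety difference

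*Protocol article*

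**What the plan says.** All references are to the protocol article.

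- **Secondary Outcomes, item 5** lists adverse effects as an outcome and gives the anticipated effects by arm: "empyrosis, itching, allergy, dizziness with moxibustion and orthostatic hypotension, headache, dizziness, and vomiting with tamsulosin". Dizziness is on both lists; the other effects are on one list only.
- **Same item, detection:** "If the patient shows any discomfort or changes in their condition, they are instructed to inform the investigators".
- **Same item, handling:** "The supervisor will manage the intervention, and any suspected AEs will be discussed with the principal investigator of the project team".
- **Blinding:** "Surgeons, moxibustion practitioners, and patients will not be blinded due to the limitation of treatment". The same sentence goes on to say that outcome assessors and statisticians are blinded.
- **Table 1** has one tick for adverse effects, in the 24 h column.
- **Statistical Methods:** "the comparison of UTI incidence, AEs, and catheterization rate will be analyzed by the chi-square test", two-sided at the 5% level.

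**The concern.** A chi-square test of AE proportions treats events as found equally well in both arms. The stated route does not secure that. It depends on what a patient who knows the treatment chooses to mention, and on what a team that also knows the treatment comes to suspect.

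The article gives reasons why reporting might lean one way. Background says alpha-blockers may cause many side effects. Discussion credits moxibustion with fewer side effects, says many Chinese patients expect it to help, and treats the placebo effect as inseparable from its efficacy.

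The events are also not specific to one treatment. Every patient has subarachnoid anesthesia and the same operation (Interventions). Headache, dizziness and vomiting can plausibly follow these in either arm, which is a general clinical assumption and not a figure in the article. If such complaints are voiced more readily by patients who took a drug, the AE comparison can favour moxibustion with no true difference. At stake is the safety statement of the trial report, not its primary result.

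**Working it through.** **1. Is there a figure in the plan to reproduce?** No. The article gives no expected AE rate and no AE sample size. The 180 per group in Sample Size concerns postoperative urinary retention only, and supplies just the number of patients here.

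**2. Inputs**

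- Patients per arm, n: 180 as planned, or 180 × (1 − 0.20) = 144 after the 20% dropout allowed for (Sample Size).
- Test: two-sided 5%, so 2.5% in each direction, critical value 1.96 (Statistical Methods).
- True AE rate p, equal in both arms: 5%, 10%, 20% (assumed).
- Capture: 100% in one arm and a share c in the other, with c = 90%, 75% or 50% (assumed).

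**3. Formula**

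Recorded rates are p₁ = p and p₂ = c·p, with mean p̄ = (p₁ + p₂)/2.

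- SE₀ = √[2·p̄·(1 − p̄)/n]
- SE₁ = √[(p₁(1 − p₁) + p₂(1 − p₂))/n]
- Chance of a significant result in the direction of the under-recording = Φ[(p₁ − p₂ − 1.96·SE₀)/SE₁]

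**4. One case in full** (p = 10%, c = 50%, n = 180)

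- Expected recorded counts: 0.10 × 180 = 18 and 0.05 × 180 = 9; p̄ = 0.075
- SE₀ = √(2 × 0.075 × 0.925/180) = 0.02776
- SE₁ = √((0.10 × 0.90 + 0.05 × 0.95)/180) = 0.02764
- (0.05 − 1.96 × 0.02776)/0.02764 = −0.16, and Φ(−0.16) = 0.437, about 44%

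**5. Chance of a false difference in that direction** (nominal 2.5%; n = 144 / n = 180)

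| True AE rate, both arms | 90% captured in one arm | 75% captured | 50% captured |
|---|---|---|---|
| 5% | 3.9% / 4.1% | 7.5% / 8.4% | 19.9% / 23.8% |
| 10% | 4.7% / 5.1% | 11.3% / 13.1% | 36.3% / 43.7% |
| 20% | 6.3% / 7.0% | 19.9% / 23.8% | 66.3% / 75.9% |

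At 90% capture the distortion is small (4% to 7%). At 75% it is 8% to 24%, and at 50% it is 20% to 76%. Within each column it grows with the true rate and with n, so more patients make the false finding more likely, not less.

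**The case against.** The strongest reply is that the article does not say reporting will differ. The reporting instruction is the same in both arms and covers any discomfort. AEs are a listed outcome with a scheduled 24 h assessment, and outcome assessors are blinded, so they may in fact be the ones recording AEs. The authors are not wholly one-sided either: tamsulosin was chosen partly because its side effects are relatively tolerable, and Discussion calls its rate of postural hypotension relatively low. AEs are the fifth secondary outcome, and the trial's case rests on urinary retention.

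Much of this stands. It keeps the point moderate and makes the percentages illustrations. It does not remove the point: an identical instruction to patients who know their treatment does not make detection equal, and the text never gives the blinded assessor the task of recording AEs.

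A reader might infer more than the article supports:

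- **That the two lists decide what is counted in each arm.** They state what patients may experience. They are neither a definition nor a collection form.
- **That the team filters events before they are counted.** The text says suspected events are discussed; it describes no filter.
- **That blood pressure is never taken, although orthostatic hypotension is named.** A condensed article commonly leaves vital signs to the full protocol, so silence here shows nothing.
- **That the list is deficient because Discussion also names syncope, or that the eligibility criteria neglect the drug's risks.** The list does not claim to be complete. Eligibility detail may also sit in the full protocol, and it is a clinical matter.

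**Conclusion.** The point holds in a limited form. As written, the plan runs a significance test on AEs whose only stated source is unprompted reporting by unblinded patients, with no common method of asking stated for the two arms. Under equal true rates of 5% to 20% and capture of 50% to 75% in one arm, a false difference in that direction would arise in about 8% to 76% of trials, instead of 2.5%. If capture differed by only a tenth, the figure would be about 4% to 7%. True rates and capture shares are assumed throughout. The article supports a likely direction, favouring moxibustion, but not a size. The primary outcome and the sample size are not affected. This is a cheap improvement to a secondary safety comparison.

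**What to change.** - Use one combined AE checklist in both arms, holding every event that Secondary Outcomes names for either treatment.
- Have the blinded outcome assessor ask it of every patient, in the same words, at the 24 h assessment already in Table 1. Take it after the urinary retention outcome has been recorded, since a patient's answers may reveal the arm.
- Record every event before anyone judges whether it is related to treatment.
- Define the compared quantity as the proportion of patients with at least one event. The chi-square test can then stay.
- If the full protocol already provides this, cite it in the article.
- The trial was ongoing at version 3.0. If patients already enrolled were not assessed this way, report AEs descriptively and state the limitation.

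**Cost:** one CRF page and a few minutes per patient. Recorded AE rates will rise in both arms, because asking finds more than waiting to be told. The checklist makes the asking equal; it cannot remove the influence of patients knowing their treatment, which should still be stated as a limitation.

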### Discontinue and Data Monitoring

Patients will be dropped if they are with the following conditions: (1) With severe adverse events (AEs); (2) Unwilling to continue the study protocol. The supervisor will make a decision to discontinue if more than 25% of the patients discontinue intervention due to AEs. Case report forms (CRFs) will be used in data collection to record demographics, assessments, and reasons for patient dropout. All CRFs will be stored in a locked cabinet. At the end of the study, the investigator will submit the CRFs to the data management committee, and the investigators cannot modify the data. The data monitoring committee is independently chaired by the Statistics Teaching and Research Office of Changshu Hospital Affiliated to Nanjing University of Chinese Medicine and claims no conflict of interest. All CRFs will be preserved for at least 5 years after publication, and access to the original data of readers and reviewers is available from the corresponding author on reasonable requests.

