### Participants

Participants will be recruited from inpatients of the Proctology Department of Changshu Hospital Affiliated to Nanjing University of Chinese Medicine, and they will be randomly assigned to either the treatment group or control group in a 1:1 ratio (Figure 1). The patients will be recruited from inpatients via posters in the department from March 01, 2021.

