### Sample Size

The sample size estimate is based on a two-arm normal design. The ratio of the two groups is set as 1:1, and the significance level of the test is targeted at 0.05, with the power achieved to detect a difference set as 0.8. According to a previous literature report, the incidence of POUR after taking tamsulosin hydrochloride was 28.1% (21). In our preliminary experiment, the incidence of POUR after moxibustion therapy is 15%. Considering the dropout rate of no more than 20%, 180 cases will be required for each group.

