### Outcome Variables

#### Primary Outcomes

*POUR incidence*: POUR is deﬁned as any of the following (21, 22): (1) patient discomfort, a sensation of a full bladder, palpable, distended bladder, with a volume of urine 400 ml; (2) any estimated postvoid residual (PVR) volume of urine greater than or equal to 200 ml per bladder scan (21); and (3) need for catheterization in 24 h.

Patients are requested to freely report the sensation of a full bladder, palpable, distended bladder at any time after the operation. The occurrence of POUR in 24 h after the operation is recorded, and POUR incidence = the number of patients who meet the diagnosis of POUR/total number of included cases in each group.

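### The drop rule does not separate stopping the intervention from leaving the study, so 24-hour inpatient outcomes that could usually be recorded may be left missing and imputed

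*Protocol article*

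**What the plan says.** Under Discontinue and Data Monitoring, the protocol article states: "Patients will be dropped if they are with the following conditions: (1) With severe adverse events (AEs); (2) Unwilling to continue the study protocol". The same section speaks of discontinuing the intervention only in the trial-level stopping rule, which applies if "more than 25% of the patients discontinue intervention due to AEs". The case report form records reasons for dropout. Nowhere does the article say whether outcomes are still collected after a patient is dropped.

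Four other places bear on the reading:

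- **Sample Size** allows for loss: "Considering the dropout rate of no more than 20" percent, giving 180 per group.
- **Statistical Methods** uses a full analysis set (FAS) and a per-protocol set (PPS). In the FAS, "for missing outcome data, multiple imputations will be used". It also tests dropout rates by arm, compares reasons for dropout and the characteristics of dropouts, and compares intention-to-treat with per-protocol results.
- **Participants** gives the setting: "Participants will be recruited from inpatients of the Proctology Department".
- **Primary Outcomes** fixes the window ("The occurrence of POUR in 24 h after the operation is recorded") and the denominator for POUR incidence ("total number of included cases in each group").

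**The concern.** The rule appears to treat the end of treatment as the end of observation. In this trial the two are easily kept apart. The patient is in a hospital bed, the primary outcome and catheterization are counted to 24 h, and urinary tract infection (UTI) is counted during the hospital stay. Stopping the intervention does not prevent staff from recording any of these.

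The loss may also be informative. Both grounds for dropping arise after randomization. Patients and practitioners are unblinded. The adverse events that the Secondary Outcomes section expects are not the same in the two arms: it lists burns, itching, allergy and "dizziness with moxibustion and orthostatic hypotension, headache, dizziness, and vomiting with tamsulosin". The Discussion notes that many patients expect moxibustion to help, so unwillingness to continue could also differ by arm. Multiple imputation as usually run assumes that outcomes are missing at random given the variables in the imputation model, which is doubtful when the reason for missingness is an adverse event or a view of the assigned treatment.

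At stake are the precision and possibly the direction of error in the primary comparison. An outcome not recorded in the 24-hour window cannot be recovered later.

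**Working it through.** **Reading the passages together.** If dropping meant only that treatment stops, outcomes would still be known and the 20% enlargement of the sample would have little purpose. With that allowance, the recording of dropout reasons and the imputation of missing outcomes, the more natural reading is that dropped patients leave with the outcome missing. The POUR denominator, however, counts all included cases, so the plan needs an outcome for the very patients whom the rule drops.

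**Inputs from the documents.** POUR 28.1% on tamsulosin and 15% on moxibustion; 1:1 allocation; power 0.8; dropout up to 20%; 180 per group (Sample Size). Two-sided 0.05, chi-square test (Statistical Methods).

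**The plan's own figure.** The usual formula with pooled variance under the null is n = [1.96·√(2·p̄(1−p̄)) + 0.842·√(p1(1−p1) + p2(1−p2))]² / (p1−p2)². With p1 = 0.281, p2 = 0.15 and p̄ = 0.2155 it gives 154 per group; the unpooled version gives 151. The stated 180 is approached (within 3%) only by multiplying by 1.2: 185 and 182. If the full allowance is used, 180 × 0.8 = 144 outcomes per arm remain, fewer than either 154 or 151.

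**Power.** Exact two-binomial power of the uncorrected chi-square test, 28.1% versus 15%, equal loss in both arms, counting observed outcomes only:

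| Loss | Observed per arm | Exact power |
|---|---|---|
| 20% | 144 | 0.781 |
| 10% | 162 | 0.824 |
| 0% | 180 | 0.864 |

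The normal approximation gives 0.774, 0.821 and 0.859.

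**Bias in an analysis of retained patients.** These inputs are assumptions, not figures from the documents: no true effect, 28.1% POUR in both arms, drops in one arm only, a fraction d dropped, and POUR risk q among the dropped. The rate seen among those retained in that arm is (0.281 − d·q)/(1 − d). For d = 0.05 and q = 0.40 this is (0.281 − 0.020)/0.95 = 0.2747, a spurious difference of 0.6 points. For d = 0.20 and q = 0.60 it is (0.281 − 0.120)/0.80 = 0.2013, a difference of 8.0 points.

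| Dropped in one arm | Spurious difference, q = 40% to 60% | Exact two-sided rejection rate |
|---|---|---|
| 5% | 0.6 to 1.7 points | 5.2% to 6.5% |
| 10% | 1.3 to 3.5 points | 5.7% to 11.3% |
| 20% | 3.0 to 8.0 points | 9.0% to 37.9% |

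If q = 28.1%, the difference is zero at every d. If the dropped had a lower risk than the rest, the sign would reverse.

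These figures apply to an analysis of retained patients, such as the PPS if it leaves out those dropped. They do not carry over to the FAS, where the bias depends on how far the imputation model fails to capture the reason for missingness.

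**The case against.** The case on the other side has several sound parts.

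- **The word is ambiguous.** The section never says that outcome recording stops or that data are discarded, and its next sentence speaks of discontinuing the intervention. A reader might infer that outcomes are thrown away. The text does not say so; the supportable statement is that they may be left missing and imputed. This is also a condensed article, and the full protocol may be clearer. The rule itself is nevertheless printed here, and what it says does not separate treatment from follow-up.
- **Treatment-related loss is not established.** The trigger is a severe adverse event, whereas the Secondary Outcomes list covers potential events without restricting them to severe ones, and dizziness appears for both arms. Neither ground requires causality. A reader might infer that drops will be treatment-related and unbalanced; the documents support only that they may be.
- **The plan anticipates dropout.** It keeps all included cases in the denominator, imputes in the FAS, tests dropout by arm and compares intention-to-treat with per-protocol results. So it would go too far to say that the FAS ceases to be an intention-to-treat analysis. These provisions stand, but they can only signal a problem; they do not supply the unrecorded outcomes.
- **Not every outcome is recoverable.** Some unwilling patients may withdraw consent or refuse the bladder scan used in one component of POUR. The 0.864 is therefore an upper limit. Drops after the third treatment, given at 24 h, cost no primary outcome.
- **20% is a ceiling.** At 10% loss power is still above 0.8, and at 5% one-sided loss the bias is small. A reader who takes only the 20% one-arm example (5.5 points at q = 50%) would overstate the problem.

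**Conclusion.** The concern holds in a limited form. As written, the rule does not distinguish stopping treatment from leaving the study, and its natural reading leaves mostly observable 24-hour outcomes missing for post-randomization reasons that may be treatment-related and may differ by arm.

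The cost in power is firm at the planning rates: between the full permitted loss and complete observation, exact power moves from below the 0.8 target to clearly above it, without one additional patient. The cost in bias is conditional. It ranges from nothing to 8.0 points over the scenarios shown, all with assumed inputs and all for retained patients only. The documents give no basis for choosing among them, nor for a figure in the FAS.

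The documents do not show that the trial discards data or that its primary analysis is invalid. If dropping was meant to end treatment only, one sentence settles the matter.

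**What to change.** Amend Discontinue and Data Monitoring to say that stopping the study intervention does not end follow-up. Then:

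- Record POUR and catheterization to 24 h, and UTI, adverse events and length of stay to discharge, for every randomized patient unless consent to data collection is withdrawn.
- Record withdrawal from the intervention and withdrawal of consent to data collection as separate items on the case report form.
- Analyse these patients in the arm to which they were randomized in the FAS.
- Keep multiple imputation for outcomes that are truly unobserved.

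The clinical decision to stop the intervention is unchanged. The cost is a short amendment and an instruction on the case report form. No extra visits are needed because the patients are in hospital. The trial was described as ongoing, so the change helps only patients not yet past their 24-hour window; for those already dropped, outcomes documented in the hospital record should be retrieved where consent allows.
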